## Abstract

**Background:**

Enhanced recovery after surgery (ERAS) programs are aimed at minimizing postoperative stress and accelerating postoperative recovery by implementing multiple perioperative principles. “Early mobilization” is one such principle, but the quality of assessment and monitoring is poor, and evidence of improved outcome is lacking. Activity trackers allow precise monitoring and automatic feedback to the patients to enhance their motivation for early mobilization. The aim of the study is to monitor and increase the postoperative mobilization of patients by giving them continuous automatic feedback in the form of a step count using activity-tracking wristbands.

**Methods/design:**

Patients undergoing elective open and laparoscopic surgery of the colon, rectum, stomach, pancreas, and liver for any indication will be included. Further inclusion criteria are age between 18 and 75 years, American Society of Anesthesiologists Physical Status class less than IV, and a signed informed consent form. Patients will be stratified into two subgroups, laparoscopic and open surgery, and will be randomized 1:1 for automatic feedback of their step count using an activity tracker wristband. The control group will have no automatic feedback. The sample size (*n* = 30 patients in each of the four groups, overall *n* = 120) is calculated on the basis of an assumed difference in step count of 250 steps daily (intervention group versus control group). The primary study endpoint is the average step count during the first 5 postoperative days; secondary endpoints are the percentage of patients in the two groups who master the predefined mobilization (step count) targets, assessment of additional activity data obtained from the devices, assessment of preoperative mobility, length of hospital and intensive care unit stays, number of patients who receive physiotherapy, 30-day mortality, and overall 30-day morbidity.

**Discussion:**

Early mobilization is a key element of ERAS. However, enhanced early mobilization is difficult to define, to assess objectively, and to implement in clinical practice. Consequently, there is a discrepancy between ERAS targets and actual practice, especially in patients undergoing major visceral surgery. This study is the first randomized controlled trial investigating the use and feasibility of activity tracking to monitor and enhance postoperative early mobilization.

**Trial registration:**

ClinicalTrials.gov identifier: NCT02834338. Registered on 15 June 2016.

**Electronic supplementary material:**

The online version of this article (doi:10.1186/s13063-017-1782-1) contains supplementary material, which is available to authorized users.

## Background

“Fast-track surgery”, or “enhanced recovery after surgery” (ERAS), is a clinical pathway for a variety of surgical procedures. The aim of ERAS programs is to minimize postoperative stress and accelerate postoperative recovery through the implementation of multiple pre-, intra-, and postoperative ERAS elements (e.g., preoperative fasting and bowel preparation or antimicrobial prophylaxis, intraoperative analgesia and fluid management, postoperative pain and drainage management, nutritional care, early mobilization) [1–3]. Nowadays, ERAS is considered standard for the perioperative management of colorectal surgical patients in many centers [4–6]. ERAS protocols have resulted in significantly shorter hospital stays and overall complications [5]. The advantages of ERAS based on the available data seem to outweigh possible disadvantages, although the quality of the data does not justify a final implementation as standard care. Nevertheless, ERAS has produced attractive results and consequently has been used in gastrointestinal (GI), hepatopancreatic, or esophageal surgery with similar results [7–12]. In recent years, ERAS programs have also been adapted to major visceral surgery of the upper GI tract [7–11]. A majority of the ERAS elements are well defined, whereas there is a lack of evidence for early mobilization protocols and monitoring. Studies on early mobilization follow different protocols and definitions. For example, Anderson et al. and Gatt et al. recommended that patients get out of bed on the day of the operation and mobilize on the floor on the first postoperative day (POD) [13, 14]. Interestingly, Anderson et al. included only patients undergoing left or right colectomy, whereas Gatt et al. included patients who underwent all kinds of colorectal operations without consideration of the severity of surgery [13, 14]. Wind et al. defined enhanced mobilization as getting out of bed more than 2 h on the day of the operation up to 8 h at the second POD after laparoscopic or open colorectal surgery [15, 16]. The findings of ERAS programs on recovery of surgical patients were subsequently transferred to ERAS programs for liver and pancreatic surgery [7, 11, 16–18]. Drawbacks of these studies are that “early mobilization” was not defined consistently and that no distinction was made between standard and early mobilization. That is why there is no solid evidence that early mobilization in the ERAS setting is beneficial. A recent study done at our center emphasizes the fact that almost 50% of our patients after surgery of the upper GI tract do not request enhanced mobilization, indicating that ERAS principles and the mobilization targets of the available studies cited above were not achieved [19].

Consequently, novel or innovative methods have to be evaluated to provide objective and precise monitoring of patient mobilization, as well as to increase the intrinsic motivation for early mobilization after major visceral surgery. One possibility could be the use of activity trackers that allow automatic feedback to patients to enhance their motivation for early mobilization. Technological progress has fostered the development of wearable devices for “self-tracking,” including the tracking of physical activity [20]. The first cohort study with 150 participants investigating the effect of a modern wearable activity trackers upon postsurgical mobility recovery during hospitalization found a significant relationship between the early recovery step count and length of hospital stay in elderly cardiac surgery patients [21]. There are no reports of randomized controlled trials (RCTs) involving activity tracking of postoperative in-hospital mobilization. The aim of the present study is to evaluate the effect of an automatic feedback system using activity trackers versus no feedback on postoperative step count and recovery after major visceral surgery.

## Methods/design

### Trial design

The Enhanced Perioperative Mobilization (EPM) trial is a randomized, controlled, single-center trial comparing the effect of automatic feedback of postoperative physical activity using activity tracker wristbands after laparoscopic and open major visceral surgery. The trial design is in accordance with the Standard Protocol Items: Recommendations for Interventional Trials (SPIRIT) statement (see Additional file 1).

### Study population

The study population consists of all patients scheduled for elective laparoscopic and open surgery of the colon and rectum (colectomy, hemicolectomy, segment resection, rectum extirpation, deep anterior rectum resection, sigmoid resection, proctocolectomy), of the stomach (total, subtotal, and atypical gastric resections), of the pancreas (any kind of pancreatic resection), and of the liver (hemihepatectomy, atypical resection, anatomical segment resection). Further inclusion criteria are age equal to or older than 18 years up to 75 years, American Society of Anesthesiologists Physical Status class less than IV, and a completed informed consent form. Exclusion criteria are emergency surgery, mental inability to complete postoperative assessment protocols, or preoperatively immobile patients. Dropout from the study is allowed in cases of nonresectability, postoperative mechanical ventilation >12 h, prolonged stay in the intensive care unit (ICU) >48 h, lack of compliance with wearing the activity tracker wrist band, or allergic reactions to the wrist band. All reasons for dropouts will be analyzed, and these patients will be followed.

The EPM trial is to be conducted in line with either the Declaration of Helsinki or the laws and regulations of Germany, whichever provides the greatest protection to the patients. The study protocol was approved by the local ethical committee of Technical University Dresden (decision number EK226062016). This study is registered with ClinicalTrials.gov under the unique identifying number NCT02834338.

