### Randomization and procedures

Patients are to be screened for eligibility on the day of admission. After participants give their informed consent to participate in the study, the International Physical Activity Questionnaire (IPAQ) will be administered to assess the preoperative mobilization, and the patients will receive preoperative counseling before surgery.

To avoid bias due to differences between laparoscopic and open surgery, two arms will be built before randomization: a laparoscopic arm and an open surgery arm. The study population will be stratified by surgery type (open and laparoscopic surgery). The randomization (control group versus intervention group) will be performed intraoperatively after the surgeon has confirmed the resectability using a block randomization with fixed block sizes in a 1:1 allocation ratio. The randomization sequences will be generated using the R statistical software package (R version 3.1.3, R Foundation for Statistical Computing, Vienna, Austria). Block size will be kept confidential until completion of recruitment.

The wristband will be worn continuously after the operation to count the patient’s steps 24 h per day until the beginning of POD 6. The Polar Loop activity tracker with FlowSync and Polar Flow software will be used for activity tracking (Polar Electro GmbH, Büttelborn, Germany). The device has been approved by the Medical Devices Act (EU Medical Device Directive 93/42/EWG/CD 0537) and is recommended for medical use.

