### Study aim and objectives

The aim of the study is to increase the postoperative mobilization of the patients by giving them continuous feedback on their step count using activity-tracking wristbands. The primary endpoint of this study is the average step count in the first five POD in the intervention and control groups. Secondary endpoints are the percentage of patients in the two groups who master the predefined mobilization (i.e., step-count) targets, assessment of the activity data obtained from the devices (distance, activity time, inactivity, calorie consumption, compliance), assessment of preoperative mobility with the IPAQ [22], length of hospital and ICU stays (from the first POD until day of discharge), number of patients who receive physiotherapy, 30-day mortality, and 30-day overall morbidity according the Clavien-Dindo classification [23].

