### Statistical considerations and sample size calculation

The sample size estimation was based on our results in a pilot study with 30 participants, 25 of whom were analyzed to collect data about standard mobilization on the first 5 PODs following major visceral surgery. Based on those data, an increase in the daily step count by 250 steps/day with an SD of 290 steps/day was estimated. To achieve 80% power with a two-sided *P* value <0.05 and a dropout rate of 12%, the total sample size calculated with a two-tailed, unpaired *t* test was 120 patients with 30 patients in each group. 

The statistical analysis will be done on an intention-to-treat basis and will be performed with Statistical Package for Social Science software version 18.0 (SPSS, Chicago, IL, USA). The Mann-Whitney *U* test will be used to compare continuous variables, and Fisher’s exact test will be used for categorical variables. Two-sided *P* values will always be computed, and a difference will be considered statistically significant at *P* ≤ 0.05. The primary outcome is the average step count over the first 5 PODs of the patients in the intervention and control goups, separated into the laparoscopic and open surgery arms, respectively. Statistical testing of the outcome parameter will be performed using a regression analysis of repeated measures. In addition, the increase of mobilization within the groups will be analyzed using the repeated measures ANOVA. Logistic regression analyses will be computed to identify factors determining the patient cohort that achieved the mobilization targets (secondary endpoint). The following variables will be considered for the regression analysis: age, sex, body mass index (BMI), operative time, oncological versus nononcological indications, type of surgery (pancreatic, liver, intestinal, gastric), preoperative IPAQ score, and technique of surgery (laparoscopic versus open). Factors that are significant in univariate analysis will be further considered for a multivariate regression analysis.

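### Dropout is allowed for events that can occur only after randomization, and the protocol does not reconcile this with its intention-to-treat analysis

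*Protocol article*

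**What the plan says.** All references are to the protocol article.

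- **Study population** lists the grounds on which dropout from the study is allowed: nonresectability, mechanical ventilation for more than 12 h after surgery, "prolonged stay in the intensive care unit (ICU) >48 h, lack of compliance with wearing the activity tracker wrist band", and an allergic reaction to the band. It adds: "All reasons for dropouts will be analyzed, and these patients will be followed".
- **Randomization and procedures** says that allocation "will be performed intraoperatively after the surgeon has confirmed the resectability". Consent and the activity questionnaire come earlier, before surgery. Control patients wear a band with a taped display; intervention patients can read theirs. A surgical fellow or study nurse visits twice daily to read the count, check use of the device and communicate feedback.
- **Study aim and objectives** makes the average step count over the first five postoperative days the primary endpoint. Secondary endpoints include "length of hospital and ICU stays (from the first POD until day of discharge", 30-day mortality and 30-day morbidity.
- **Statistical considerations and sample size calculation** states: "The statistical analysis will be done on an intention-to-treat basis". It also allows for 12% dropout in reaching 120 patients, and it plans a repeated-measures regression for the step count.
- **Study implementation** plans a day-30 visit at which data on all endpoints are gathered.

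**The concern.** Four of the five dropout reasons follow allocation. Two of them, long ventilation and a long ICU stay, mark patients who will walk little, so they are tied to the primary outcome. A third, not wearing the band, concerns the study device itself, which differs between arms in whether the patient can read it. Dropout is permitted and not mandatory, and the article describes no masked or fixed rule for declaring non-compliance. The people checking the band can see which arm the patient is in.

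If such patients leave the analysis, the step-count comparison is no longer between the groups that randomization formed. If they also leave the secondary analyses, ICU stay is selected on its own value, and morbidity and mortality are compared only among patients with a good early course. As written, either analysis set could be defended after the data are seen.

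**Working it through.** **1. Timing of each dropout reason**

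| Reason | When it can occur | Consequence |
|---|---|---|
| Nonresectability | After consent, before allocation | Coherent as a pre-randomization exit |
| Ventilation >12 h | After allocation | Tied to low step count |
| ICU stay >48 h | After allocation | Tied to low step count; also the value of a secondary endpoint |
| Band non-compliance | After allocation | Could differ by arm |
| Band allergy | After allocation | Ends measurement |

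**2. The plan's sample size**

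Inputs from the statistical section: difference 250 steps/day, SD 290, two-sided 0.05, power 80%, dropout 12%.

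- Unpaired *t* test, d = 250/290 = 0.862: 22.1, so 23 per group.
- With dropout: 23/(1 - 0.12) = 26.1, so 27 per group, or 4 x 27 = 108.
- The stated figures are 30 per group and 120 in total. They are not reproduced, but the difference is on the conservative side and does not affect this point.
- Patients covered by the allowance: 0.12 x 30 = 3.6 per group; 0.12 x 120 = 14.4 in total. The article does not divide the 12% by reason.

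**3. When removal biases the step count**

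Suppose there is no true effect and both arms have mean M. If a fraction q of an arm, with mean L, is removed, the remaining mean is (M - qL)/(1 - q). The values below are assumptions for illustration and do not come from the article: M = 600 steps/day, L = 0 to 200.

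| Removed, control / intervention | L = 200 | L = 0 |
|---|---|---|
| 12% / 12% | 654.5 - 654.5 = 0 | 681.8 - 681.8 = 0 |
| 8% / 16% | 676.2 - 634.8 = +41 | 714.3 - 652.2 = +62 |
| 4% / 20% | 700.0 - 616.7 = +83 | 750.0 - 625.0 = +125 |

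Differences are intervention minus control. Swapping the arms reverses every sign. Equal removal of like patients gives zero; unequal removal gives an error whose sign depends on which arm loses more. The article supplies none of q, L or M, so no row is an estimate for this trial.

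**4. Whether 120 patients can carry a full intention-to-treat analysis**

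*t*-test power within one surgical stratum, SD 290:

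- All 30 per group analysed, effect 250: 90.7%.
- 12% removed (30 x 0.88 = 26.4, taken as 26 per group), effect 250: 86.2%.
- All 30 analysed, 12% assumed to gain nothing (0.88 x 250 = 220), SD unchanged: 82.4%.

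The last case has little room. With 30 per group, 80% power needs d = 0.736, so at an effect of 220 the SD may rise to about 220/0.736 = 299 before power falls below 80%.

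**The case against.** The strongest reply is that the article never says these patients are excluded from an analysis. It commits to intention to treat, follows dropouts, and gathers all endpoints at day 30. Intention-to-treat trials commonly inflate for missing outcomes, and a patient without a band has no step count. Analysis sets and missing-data rules are often left to an analysis plan. Ventilation and early ICU stay are unlikely to be changed by a step display, so those losses may be roughly balanced.

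Much of this stands, and it rules out several stronger readings that a reader might infer:

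- **That dropouts are lost to the ICU, morbidity and mortality comparisons.** This is a possible reading, not a stated rule; the follow-up sentence and the day-30 visit point the other way.
- **That a bias of a given size or sign can be quoted.** It cannot. More control dropout is conceivable because the taped band tells the wearer nothing, but the article gives no rates, and step deficits that suit ICU patients need not apply to non-wearers.
- **That the 14 or so patients are mainly the sickest.** The 12% is not split by reason and may include allergy and non-compliance.
- **That listing nonresectability is an error.** It is a coherent exit between consent and randomization.
- **That the ICU clock should start at the end of surgery.** That is a separate choice of endpoint definition.

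What the reply does not remove is the conflict itself. The article states a dropout rule based on post-allocation events and an intention-to-treat rule, and does not say which governs. It promises to analyse the reasons for dropout and to follow the patients, but following them is not the same as analysing their outcomes. This goes beyond detail deferred to another document.

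**Conclusion.** The point holds as an unreconciled conflict over who is analysed. Four dropout reasons can arise only after randomization, at least two are tied to the outcome and one to compliance, and staff who know the allocation may apply them at discretion. The 12% allowance, about 14 of 120 patients, suggests that dropouts are expected to be missing from the primary analysis, but does not prove it.

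Bias in the step count is possible and depends on removal differing by arm in rate or type. Its direction is unknown and its size cannot be derived from the article. Harm to the secondary endpoints is conditional on dropouts being left out there too; in that case ICU stay is cut at its own 48 h threshold, and 30-day morbidity and mortality lose the sickest patients.

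**What to change.** Before any results are seen, state that:

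1. Ventilation >12 h, ICU stay >48 h, band non-compliance and band allergy may end band wear but do not remove a randomized patient from any analysis.
2. The step count is analysed as randomized, using every recorded day in the planned repeated-measures regression, fitted by a likelihood-based method. Days of non-wear are set to missing and not counted as low; days recorded in the ICU keep their counts.
3. ICU stay, hospital stay, morbidity and mortality are analysed in all randomized patients.
4. The analysis without dropouts is reported only as a sensitivity analysis.
5. Nonresectability applies only before randomization.

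The cost is mainly wording and a small analysis change: the protocol already follows these patients, and device compliance is among its endpoints. The downside is slightly more variable step counts and some dilution of the effect. Power stays at or above 80% per stratum under the assumptions shown, with little margin if the SD rises as well.

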### Randomization and procedures

Patients are to be screened for eligibility on the day of admission. After participants give their informed consent to participate in the study, the International Physical Activity Questionnaire (IPAQ) will be administered to assess the preoperative mobilization, and the patients will receive preoperative counseling before surgery.

To avoid bias due to differences between laparoscopic and open surgery, two arms will be built before randomization: a laparoscopic arm and an open surgery arm. The study population will be stratified by surgery type (open and laparoscopic surgery). The randomization (control group versus intervention group) will be performed intraoperatively after the surgeon has confirmed the resectability using a block randomization with fixed block sizes in a 1:1 allocation ratio. The randomization sequences will be generated using the R statistical software package (R version 3.1.3, R Foundation for Statistical Computing, Vienna, Austria). Block size will be kept confidential until completion of recruitment.

The wristband will be worn continuously after the operation to count the patient’s steps 24 h per day until the beginning of POD 6. The Polar Loop activity tracker with FlowSync and Polar Flow software will be used for activity tracking (Polar Electro GmbH, Büttelborn, Germany). The device has been approved by the Medical Devices Act (EU Medical Device Directive 93/42/EWG/CD 0537) and is recommended for medical use.

The control group will wear an activity tracker wristband with a display covered with adhesive tape so that the step count cannot be read. The study nurse will verify the covered display a few times daily. The intervention group will receive an unblinded wristband. The handling of the activity trackers will be explained to the patients, and a predefined mobilization endpoint (step count) for the first 5 PODs will be targeted. The target step count was set at the 85% quartile on the basis of results a previous pilot study (Table 1). Patients older than 75 years of age were excluded from the analysis in the pilot study. The median age of this group was 60 years (IQR 52.5–70.5 years). A major pancreatic resection was performed in 35% of the patients, a major liver resection in 30%, a colorectal resection in 25%, and a gastric resection in 10%. A surgical fellow or a study nurse will assess and monitor the patient twice daily, between 9:00 a.m. and 11:00 a.m. and between 3:00 p.m. and 5:00 p.m., throughout the patient’s hospital stay to read the step count, to ensure its proper use and functioning, and to communicate the automatic feedback results. The study flowchart is shown in Fig. 1.

**Table 1 Tab1:** Mobilization targets in steps per day

	POD 1	POD 2	POD 3	POD 4	POD 5
Open surgery arm (*n* = 20)	500	620	800	1400	1400
Laparoscopic arm (*n* = 5)	1900	2300	2900	3400	3400

*POD* Postoperative day

Data are presented as 85% quartile based on *n* = 25 patients (results of a pilot study)

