### Study implementation

Patients will be assessed daily by a surgical fellow or a study nurse throughout their hospital stay. The whole team, including nurses and physiotherapists, is trained for the mobilization with the study patients and assists the patients on the arm without the activity-tracking device to avoid bias. The data obtained from the activity tracker will be synchronized automatically at POD 6 according to the user manual. The team will also follow the patients after their discharge and perform all data collection in an attempt to minimize observer bias. All outcome parameters will be recorded before the operation and on PODs 1, 2, 3, 4, and 5. At a follow-up visit on POD 30, data on all endpoints and patient characteristics will be gathered. Figure 2 shows the study implementation in accordance with the SPIRIT statement.

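### Fixed block sizes with visible arms at one centre leave a modest, avoidable share of allocations predictable; keeping the size confidential and randomising in theatre only partly cover this

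*Protocol article*

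**What the plan says.** All but two of these statements are in the protocol article under Randomization and procedures.

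- **Scheme.** Allocation is made "using a block randomization with fixed block sizes in a 1:1 allocation ratio". The size itself is not stated.
- **Strata.** "The study population will be stratified by surgery type (open and laparoscopic surgery"), which gives two separate sequences. With 30 patients in each of four groups, each sequence has 60 places.
- **Safeguard 1.** "Block size will be kept confidential until completion of recruitment".
- **Safeguard 2.** The draw "will be performed intraoperatively after the surgeon has confirmed the resectability", whereas "Patients are to be screened for eligibility on the day of admission". Consent is therefore obtained before the arm is drawn.
- **Visibility.** "The intervention group will receive an unblinded wristband", while controls wear the same device with its display taped over. A surgical fellow or study nurse visits twice a day.
- **Setting.** Trial design describes a "randomized, controlled, single-center trial". Under Study implementation, "The team will also follow the patients after their discharge and perform all data collection".

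The article does not say who approaches patients, who holds the list or how an allocation is released to theatre.

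**The concern.** In a permuted block of fixed size, the last places are determined once one arm is full. Anyone who knows the size and has followed the stratum then knows the next arm before it is drawn. The usual conditions for this are present: one centre, only two short sequences, and arms that anyone can read off the wristband.

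Two discretionary steps come before the draw. One is the decision whom to approach at admission. The other is the judgement of resectability in theatre, immediately before allocation. If either were influenced by an expected arm, the groups could differ in fitness or motivation, on which a step count plausibly depends. The Discussion itself accepts that differences in functional ability may bias the study. Selection of this kind happens before randomisation, so the planned intention-to-treat analysis would not correct it.

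**Working it through.** The plan gives no figure for predictability, so there is nothing to reproduce. The inputs from the article are 1:1 allocation, fixed blocks, two strata and 60 patients per stratum (120 / 2). The block size is assumed, over the range 4 to 10.

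**1. Size known to the observer (exact).** Write the block size as 2m. The expected number of forced places per block is 2m/(m+1), so the certain share is 1/(m+1). The success rate of always guessing the arm with more places left is [m + (2^(2m)/C(2m,m) − 1)/2] / 2m.

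| Block size | Certain share | Per stratum of 60 | Best-guess success |
|---|---|---|---|
| 4 (m=2) | 1/3 = 33.3% | 20 | [2 + (16/6 − 1)/2]/4 = 70.8% |
| 6 (m=3) | 1/4 = 25.0% | 15 | [3 + (64/20 − 1)/2]/6 = 68.3% |
| 8 (m=4) | 1/5 = 20.0% | 12 | [4 + (256/70 − 1)/2]/8 = 66.6% |
| 10 (m=5) | 1/6 = 16.7% | 10 | [5 + (1024/252 − 1)/2]/10 = 65.3% |

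The certain share keeps falling as blocks grow: 9.1% at size 20, and 3.2% if the whole stratum were one block of 60.

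**2. Size fixed but confidential, as the protocol specifies (simulation).** The observer starts with equal weight on sizes 2, 4, 6, 8, 10 and 12, sees every past allocation in one stratum of 60, and updates by Bayes' rule. A prediction counts when its probability exceeds 95%.

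| True size | Callable with >95% certainty | Median patients until the true size has >95% posterior |
|---|---|---|
| 4 | about 20% (0.20 × 60 = 12) | 42 |
| 6 | about 14% (0.14 × 60 ≈ 8) | 42 |
| 8 | about 11% (0.11 × 60 ≈ 7) | 36 |
| 10 | about 11% (≈ 7) | 24 |

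Confidentiality therefore lowers the share, for example from 33% to 20% at size 4, but does not bring it near zero. Some near-certain calls do not require the size to be settled.

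**3. Randomly varied sizes, with the set known but not the order (simulation, stratum of 60).**

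| Set of sizes | Certain share | Best-guess success |
|---|---|---|
| 4, 6 | about 5.6% | about 69% |
| 2, 4, 6 | about 4.1% | about 70% |
| 4, 6, 8 | about 2% | about 68% |

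Applying the >95% threshold of step 2 instead of strict certainty gives practically the same shares (5.5%, 4.1% and 2.2%), so steps 2 and 3 can be compared directly.

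**4. Comparison.** Near-certain calls fall from about 11–20% (fixed, confidential) to about 2% (4/6/8). Best-guess success is 65–71% for fixed sizes 4 to 10 and 68–70% for the varied sets, so it is essentially unchanged.

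**The case against.** The protocol does not ignore the problem. It withholds the block size, and it draws the arm late, after consent and after resectability is confirmed. To exploit a prediction at admission, staff would have to foresee the order in which patients in that stratum reach randomisation, including who proves nonresectable. The study population is also defined as all patients scheduled for the listed operations, which limits formal discretion over whom to approach. Nothing shows that the people who approach patients keep a tally of earlier allocations, and a journal article may leave concealment logistics to the full protocol.

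Much of this stands. It rules out several stronger statements that a reader might infer:

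- **That a third or a quarter of allocations are open to prediction.** Those shares hold only for a known size of 4 or 6, and the protocol keeps the size confidential.
- **That the size becomes obvious after a few blocks.** At size 4 the median is 42 patients, more than ten blocks. Only larger sizes are learned in fewer blocks, and at those sizes fewer places are forced.
- **That randomising in theatre makes no difference.** It narrows the opportunity at admission. It does less for the resectability judgement, where the next place in the stratum is the current patient's and no theatre order has to be foreseen.
- **That a bias in steps per day can be stated.** The documents give no difference between favoured and other patients. Any such figure would be invented, and it would scale with best-guess accuracy, which varied blocks barely alter.

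**Conclusion.** The point holds as a minor design improvement. Fixed blocks, visible arms and a single centre leave a modest and avoidable risk that the stated safeguards reduce but do not remove. Its size is about 11–20% of allocations callable with over 95% certainty. This assumes block sizes 4 to 10, an attentive observer who sees all allocations in one stratum of 60, and equal initial weight on the candidate sizes. The share would be higher if the size leaked (20–33% for sizes 4 to 8) and only a few percent if the blocks were very large.

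That enrolling staff overlap with those who see the wristbands is plausible at one centre but not stated. A reader should not infer that selection has occurred or that the primary comparison is biased; the documents show neither. Nor is the protocol contradictory here.

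**What to change.** For patients still to be randomised, generate the remaining sequence in each stratum with randomly varying block sizes, for example 4, 6 and 8. State only that sizes vary, and withhold both the set and the order from clinical staff. Even if the set became known, about 2% of allocations would be near-certain (about 6% with 4 and 6 only). The change does not make guessing useless, since a best guess would still be right about 68% of the time.

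The cost is a few lines in R, which the trial already uses for its lists, and a short amendment. Trial status reports recruitment as ongoing, so the change could apply to the remaining patients. The downside is a slight imbalance within a stratum if recruitment stops mid-block: at most 4 patients with a block of 8, against at most 2 with a block of 4.
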